##### Delivery of educational articles

According to the IMB model, if a patient possesses the requisite adherence information, they are more likely to enact specific adherence behavioural skills and exhibit behavioural change. Thus, during the 6 months of the intervention period, a series of educational articles containing ART-adherence information and adherence skills are delivered automatically and freely to the participants via the WeChat official account.

The content of the educational articles was developed based on a literature review, individual interviews, and group discussions. For instance, qualitative interviews of ART-experienced MSM were conducted to discuss the health concerns and information they needed most during their initial 6 months of ART. According to the needs expressed by interviewees, different topics of educational articles were derived, and approximately 1400 educational articles were subsequently collected from social media accounts. Six trained medical undergraduates worked in pairs to read and screen these articles for comprehensibility and timeliness. The final selection of 209 articles was authorized by the authors and then edited to add illustrations and remove sensitive words (e.g. HIV/AIDS) from the titles to avoid inadvertent disclosure of HIV status. Then, the modified articles were examined by physicians to ensure the information was valid and timely. The articles spanned 13 topics related to aspects such as adherence, side effects, and mental health. Detailed information on the contents of the articles is shown in Table 2.

**Table 2 Tab2:** Educational article topics

Topic of articles	Numbers	Topic of articles	Numbers
Adherence	6	Laws and regulations	19
Basics about HIV and ART	14	Mental health	10
Comorbidities	33	Notes about medication taking	10
Daily life	46	Other concerns	5
Disclosure	4	Side effects	19
Drug resistance	8	Transmission prevention	9
Interpretation of test results	14	–	12

To improve the accessibility and effectiveness of the intervention, the time and frequency for supplying information to participants was considered. In terms of timing, it was decided to send the educational material to participants at 10 p.m. to optimize subjects’ assimilation of the information. This timing was for three reasons: 1) a previous study had suggested that the rate of reading articles published on WeChat accounts peaked at 10.00 p.m. [43]; 2) individual MSM patients had suggested in interviews that educational articles should be delivered at night to avoid inadvertent sero-status disclosure to colleagues in the daytime or to friends during off hours. 3) case managers also recommended 10:00 p.m. for article-delivery, as this would be close to most patients’ daily medication-taking schedule, i.e., half an hour before patients’ bedtime.

The frequency of articles delivered are different over time to avoid inciting negative behaviours among the participants [44]. Thus, in the first 2 weeks of month one, educational materials are sent to the participants daily, and then for the second 2 weeks of month one, they are sent three times per week. After this, two articles are delivered per week in the following 2 weeks, and then once per week for the rest of the intervention period. Currently, 132 participants have been assigned to the intervention group and a total of 44 articles have been sent to this arm, with an average of 112 reading times for each article. Participants can also retrieve previous published articles at any time, with instructions on retrieval reiterated in monthly reminders.

##### Individual online communication

One-to-one online communication can be initiated by participants or nurses to provide social and instrumental support during the process of ART. Participants can send messages to the nurse case managers if they have any question regarding ART, and nurses are requested to promptly respond to the inquiries, i.e., within 2 days. In addition, automatic messages are sent to each participant asking about their medication-taking behaviours and mental health status at day 7 and day 14 after ART initiation, which were suggested by case managers as being important time points for identification of non-adherent behaviour and to improve adherence.

The purpose of these nurse–participant interactions is to evaluate participants’ progress and help identify barriers to progress, and nurses are required to provide tailored feedback and personalized information to an enquiring patient. If a patient expresses negative emotions during the individual online communication, the case managers will, if necessary, provide emotional comfort and counselling. Considering the feasibility of intervention, the numbers of messages that patients can send are limited to a certain level to balance the workload of case managers and the needs of patients.

##### Hospital-visit reminders

A message-reminder module for hospital visits was designed to run autonomously, to facilitate patients’ medication-taking and retention in the ART program. Four follow-up hospital visits are scheduled at months 1, 2, 3 and 6 after ART initiation. Case managers and patients discuss and agree on an exact date for each hospital visit at patients’ convenience. The reminder messages are sent 7 days prior to each scheduled hospital visit. The wording of the reminders is intentionally vague to avoid unwanted disclosure of HIV infection.

##### Supportive service information

The IMB model suggests that psychological functioning (e.g., depression) and access to care might moderate the associations between predictors and adherence outcomes [31]. Thus, in this study we provide easily accessible linkage and referrals to supportive services, including psychological counselling, sexually transmitted diseases (STD) treatment, detoxification, LGBT support (from an NGO), amongst others. Interviews with staff of psychological institutes, NGOs, and detoxification service centres revealed major variations in services provided by different organizations in terms of cost and approach, and the complexity that would arise if those services were all to be provided in our program.

Therefore, information regarding the location, opening hours, and potential charges of these supportive service institutions are collated and sent to patients monthly via WeChat, as a module of interventions delivered in the present study. Patients can also easily require services from relevant organizations using the WeChat platform. The flow chart is shown in Fig. 2.

**Fig. 2 Fig2:**
[figure not shown]
Flow chart of the trial

### Pilot study

A 1-month pilot study was conducted among 20 participants to assess the feasibility and acceptance of intervention, and detect potential problems in wording or length of the questionnaire, thus providing information that might help to optimize the design of the intervention. Thus, some questionnaire wording was revised after the pilot study, and the limit on the number of messages that could be sent by patients was adjusted according to patients’ feedback. During the initial pilot phase, the nurse case managers were observed and supervised in the whole process of recruitment and implementation, and were advised if they displayed any inappropriate expressions or behaviours, e.g., exaggerating the benefits of the intervention or recommending other health information resources to participants. An additional training session were delivered to case managers to strengthen the SOP after the pilot study.

### Patient and public involvement (PPI)

PPI representatives worked with us to develop and refine the design of the intervention. However, it was difficult to involve patients in other areas of the study due to data protection restrictions. Patients were not consulted to develop patient-relevant outcomes or interpret the results. Patients were not invited to contribute to the writing or editing of this document for readability or accuracy.

### Data collection

Baseline assessment is initially being conducted at the enrolment procedure on a tablet, under the instruction of investigators. Data on demographic characteristics (age, marital status, education, monthly income, employment, and eHealth literacy), HIV status (transmission route, duration after diagnosis, sexual orientation, sero-status disclosure, STDs), psycho-social conditions (mental health, quality of life, illness representation, perceived stigma, social support, IMB constructs) and risky behaviours (sexual and drug use behaviours) are collected.

Follow-up assessments will be scheduled at months 1, 3, 6 and 12 (6-month post-intervention). The content of follow-up assessments at each time-point is described in Table 3, and covers variables related to ART adherence, mental health, illness representation, sexual risk behaviour, IMB constructs and quality of life. The links to the online questionnaire will be sent to all participants automatically via WeChat, and they can fill in the questionnaire on any electronic device, such as smartphones. Questionnaires are checked weekly and reminder messages are sent to participants who have not completed the questionnaires in the required time. If the reminders have been sent twice and ignored twice, a phone call will be made to participants. Participants can receive an online cash transfer of 10 Chinese Yuan (CNY), 20 CNY and 20 CNY (50 CNY in total, which equals approximately 7 US dollars) if they finish the follow-up questionnaires in each of months 3, 6 and 12.

**Table 3 Tab3:**
[figure not shown]
Schedule of enrolment, interventions, and assessments

### Measures

#### Primary outcome

The primary outcome of this study is self-reported ART medication adherence and CD4 count at month six. As literature studies have shown that self-reported adherence is usually positively skewed, mostly due to social desirability bias and recall bias [45], we adopt a composite scale that has high sensitivity [46]. This scale consists of three adherence items measuring medication-taking adherence in the preceding 30 days: 1) a ‘days missed’ item, in which participants are asked the number of days they have missed an ART dose; 2) a ‘rating’ item, in which participants are asked to rate their pill-taking performance; 3) a ‘frequency’ item, in which participants are asked how frequently they took their pills according to instructions. Cronbach’s alpha was 0.86 in the previously reported study using this scale [47]. Moreover, item responses for the three adherence items were linearly transformed to a 0–100 scale and the average scores of all three items are used. A summary of the individual adherence items was calculated as the mean of the three individual items. In this study, we consider anyone scoring below the maximum score on any item as non-adherent (i.e., a combined scale score of < 100). CD4 counts are examined in each physical test and measured by flow cytometer. The months one and three assessments allow for trend evaluation and the month 12 assessments will allow for evaluation of persistent effect of intervention, but these are not the primary outcomes.

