#### Recruitment, enrolment and randomization

Potential participants are being recruited from the collaborative hospital that provides ART for PLWHA. Four nurse case managers with previous experience of case management are responsible for participant recruitment and intervention delivery. Before the commencement of this study, all nurse managers received two four-hour training sessions on recruitment, data collection, intervention specification, and tutoring about the APP. After nurse case managers confirm their eligibility and obtaining written informed consent, participants are invited to complete baseline assessments and then randomly assigned to intervention (SOC + mHealth) or control groups (SOC) in a 1:1 allocation ratio. Block randomization (block length = 4) is adopted and random numbers are generated with SAS 9.4.

Written records of group-assignments are sealed in individual opaque envelopes marked with study identification numbers. The intervention group then receive brief training in use of the WeChat program official account from the investigators and are reminded to not forward the WeChat platform to others, to avoid potential confounding effects. Both the control and intervention group are required to ‘friend’ the research team’s WeChat account for data collection and to provide user feedback. Participants’ enrolment information including name, research ID (RID), medical ID, phone number, and their case managers, are documented. The research ID is composed of a skewed date (month plus one) and the sequence of the intraday enrolment to ensure confidentiality. All participants are encouraged to refrain from seeking other health interventions during the active study period. Standard operating procedure (SOP) and program manuals have been developed to guide the study.

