### Sample size estimation

We will calculate the size of effect that the sample size in our study can detect with 80% power (two-tailed alpha 0.05) with regard to the primary outcome. Based on previous studies conducted among Chinese MSM that newly initiate ART, we estimate that the adherent rate at month six in the control group will be 89% [14]. The target sample size of 600 (300 in each arm) will be powered to detect a smallest between-group difference of 9% in adherent rates, allowing for a 20% attrition rate at month six.

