#### Effectiveness of intervention

The primary outcomes will be the prevalence of ART adherence and CD4 counts at month six. For the between-group comparisons, *χ*^*2*^ test will be used for binary outcomes (e.g., ART adherence, mental health disorders, sexual risk behaviours) and *t*-test for continuous outcomes (e.g., CD4 count, quality of life, illness representation, IMB constructs, and HIV viral load). Within-subject analyses will also be conducted, comparing the baseline response to follow-up session responses.

Intervention effects will be performed on the principle of intention-to-treat (ITT), using the data collected from all randomized participants in the analysis. Missing endpoints will be imputed by Multiple-Imputation approach. The General estimating equation (GEE) will be used for repeated measures analyses using SAS 9.0, which allows for the inclusion of all subjects in the analysis regardless of their number of visits. As GEEs require data to be randomly missing, the analysis will be repeated using a subset of participants with complete data. A sensitivity analysis will be conducted to determine the impact of dropout and to evaluate additional longer timeframes (month 12).

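### Two primary outcomes at month 6, one two-sided 0.05 assigned to adherence alone, and no rule saying whether one or both must succeed

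*Protocol article*

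**What the plan says.** The Primary outcome section of the protocol article states: "The primary outcome of this study is self-reported ART medication adherence and CD4 count at month six". The Effectiveness of intervention section repeats the pair in the plural: "The primary outcomes will be the prevalence of ART adherence and CD4 counts at month six". The Abstract also names both. The analysis section assigns adherence to the chi-square test and CD4 count to the t-test, and describes no joint test.

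The Sample size estimation section then works with one outcome. It seeks the effect that the trial "can detect with 80% power (two-tailed alpha 0.05) with regard to the primary outcome", and from there uses adherence only: "we estimate that the adherent rate at month six in the control group will be 89" per cent, and "The target sample size of 600 (300 in each arm) will be powered to detect a smallest between-group difference of 9% in adherent rates". A loss of one fifth of participants by then is built in. It gives no alpha, effect size, standard deviation or power for CD4. No section says whether success needs one outcome or both, which is tested first, or how alpha is shared.

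**The concern.** The number of primary outcomes differs between sections: two where outcomes and analysis are described, one where alpha and power are set. The success rule links the two, and it is absent. Without it, neither the 5% error rate nor the 80% power can be attached to the trial's conclusion.

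The two outcomes could well disagree. Adherence is self-reported in an open-label trial, and the Discussion accepts that participants' awareness of the intervention might bias results. CD4 is offered there as an objective indicator. If one is significant and the other is not, the text as it stands lets the choice of which one carries the claim of efficacy be made after the results are known.

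**Working it through.** **Inputs.** Two primary outcomes with separate tests (Primary outcome; Effectiveness of intervention). Two-sided alpha 0.05, 80% power, control adherence 89%, a 9-point difference, 300 per arm and 20% attrition (Sample size estimation). Allocation "in a 1:1 allocation ratio" (Recruitment, enrolment and randomization). Evaluable per arm: 300 × (1 − 0.20) = 240. Assumed, because the article does not say: CD4 is tested at two-sided 0.05, and the correlation r between the two test statistics ranges from 0 to 0.9.

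**The plan's own figure.** For a pooled chi-square test of p1 against p2 with mean p̄, difference d and n per arm,

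power = Φ{ [d√n − z(1−α/2)·√(2p̄(1−p̄))] / √(p1(1−p1) + p2(1−p2)) }.

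For 89% versus 98%, p̄ = 0.935, √(2 × 0.935 × 0.065) = 0.3486 and √(0.0979 + 0.0196) = 0.3428. At α = 0.05 and n = 240: (0.09 × 15.492 − 1.960 × 0.3486) / 0.3428 = 2.07, so power is 98.1%. The smallest increase from 89% detectable with 80% power is 6.8 points (7.1 with continuity correction). The stated 9 points is therefore not reproduced for an increase. A fall from 89% comes close, with a detectable difference of 9.3 points. That is a separate matter and does not affect the false-positive rate.

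**Error rate if either outcome suffices, each at 0.05.** Under independence: 1 − 0.95² = 9.75%. For correlated statistics, 1 − P(|Z1| < 1.96 and |Z2| < 1.96) under a bivariate normal distribution:

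| r | Either significant | Both significant |
|---|---|---|
| 0 | 9.75% | 0.25% |
| 0.2 | 9.6% | 0.4% |
| 0.5 | 9.1% | 0.9% |
| 0.7 | 8.3% | 1.7% |
| 0.9 | 7.0% | 3.0% |

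The upper bound is 0.05 + 0.05 = 10%, and the rate falls to 5% only as r approaches 1.

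**Error rate if both are required.** The table's last column applies when neither outcome is affected. If one is truly affected and the other is not, the chance of a false joint claim is still at most 5%.

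**Power if both are required.** Joint power cannot exceed the CD4 test's power, which cannot be computed. With 98.1% for adherence and independence, joint power reaches 80% if CD4 power is at least 0.80 / 0.981 = 82%.

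**Cost of splitting alpha.** At 0.025 each, the familywise error is 1 − 0.975² = 4.94% under independence and never above 5%. For 89% versus 98% with 240 per arm: (1.3943 − 2.241 × 0.3486) / 0.3428 = 1.79, so power is 96.3%. This needs 142 evaluable per arm, and 142 / 0.80 = 178 after attrition, against 300 planned. The smallest detectable increase at 80% power goes from 6.8 to 7.3 points.

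**The case against.** The strongest reply is that this is an omission, not an error. A multiplicity rule often sits in the statistical analysis plan, which is not shown, and an article condenses. Sizing on one primary outcome at 0.05 also fits a fixed sequence or a both-required rule, so the sample size section is not wrong in itself. This stands in part: an unseen plan may contain a rule. It does not remove the inconsistency between two declared primaries and a design statement that refers to one. The success rule determines what the stated alpha and power mean, so it has to agree with them.

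A reader might infer that the trial's false-positive rate simply is 9.75%. The documents do not support that. The figure needs either outcome to count as success, CD4 to be tested at 0.05, and independent tests, and none of these is stated. The singular wording that joins adherence and CD4 can equally be read as requiring both.

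A reader might also infer that the 80% power fails if both are required. That is not shown. CD4 power is unknown, and the adherence test has more than 80% power at the protocol's own 9 points.

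Nor is a split alpha expensive, as one might think from calculating at the 6.8-point limit, where power drops from 80% to 71%. At 9 points it stays at 96.3%.

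**Conclusion.** The point holds in conditional form. The article declares and separately tests two primary outcomes, assigns the only stated alpha to adherence, and leaves the success rule open.

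- If either suffices and CD4 is tested at 0.05, the familywise error exceeds the nominal 5% and can approach 10%. A positive correlation between adherence and CD4 is plausible, in which case 9.75% is close to a ceiling.
- If both are required, error is controlled, but the design statement says nothing about the chance that the trial succeeds, because CD4 has no planning assumptions.

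The error rates rest on a bivariate normal approximation to the two test statistics. The adherence figures rest on the article's 89%, 9 points and 20% attrition.

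**What to change.** Before the data are analysed, state one rule, in the same terms, in the Sample size estimation and Effectiveness of intervention sections, and make the number of primary outcomes agree throughout. Either of these controls the familywise error at 5% without extra participants:

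- **Fixed sequence.** Test adherence at month 6 first at two-sided 0.05. Test CD4 at month 6 at 0.05 only if adherence is significant; otherwise report CD4 as an estimate with a confidence interval and make no confirmatory claim. The stated alpha stays as it is and adherence loses no power. The cost is that CD4 alone cannot make the trial positive, and the objective outcome sits behind a self-reported one in an open-label trial.
- **Split alpha.** Use 0.025 for each outcome, or Holm. Both remain primary and either can support a claim. The cost is the rise of about half a point in the smallest detectable adherence increase shown in the working.

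Requiring both is also valid without adjusting alpha, but it calls for a CD4 effect size and standard deviation, so that power can be stated for the joint criterion. The choice is for the sponsor. What matters is that it is written down before results are seen.

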#### Secondary outcomes

***HIV-1 RNA*** viral load at month 12 was measured by polymerase chain reaction (PCR).

***Mental health*** status includes anxiety and depression, which are measured by the seven-item Generalized Anxiety Disorder-7 (GAD-7) instrument [48] and nine-item Patient Health Questionnaire-9 (PHQ-9) [49], respectively. Both instruments comprise four-point Likert scales with the responses based on occurrence of symptoms during the last week. In each scale, the sum of all items will be calculated and categorized into different levels of mental health disorder: normal (0–4), mild (5–9), moderate (10–14), and moderate to severe (≥15) [50, 51].

***Quality of life*** is measured by the 31-item HIV adaptation of the World Health Organization Quality of Life scale (WHOQOL-HIV bref) [52], which has shown good reliability and validity among Chinese PLWHA [53]. The scale consists of six domains: physical health, level of independence, psychological health, spirituality, social relations and environmental health. For each domain, a score ranging from 4 to 20 will be calculated, with higher scores denoting better quality of life.

***Illness representation*** is measured by the Brief Illness Perception Questionnaire (B-IPQ), which has been used among PLWHA to evaluate their cognitive and emotional response towards HIV [54]. The B-IPQ comprises the following eight dimensions: consequences, timeline, personal control, treatment control, identity, coherence, concern, and emotional response. Each dimension has only one question, with responses rated on a scale from 0 to 10. A higher score indicates a greater perception of a threat from HIV [55].

***ART-related perception*** is measured by the Life Windows Information-Motivation- Behavioural Skills ART Adherence Questionnaire (LW-IMB-AAD) [56]. The instrument consists of 33 items rated on a 5-point Likert scale, with nine measuring information, ten measuring motivation, and 14 measuring behavioural skills. Summative scores are computed for each aspect, with higher scores reflecting better information, motivation and behavioural skills about adherence [57].

***Sexual risk behaviour*** before and after diagnosis is measured separately using self-constructed items, including numbers of male/female and regular/casual partners, and frequency of condom use. Example items include, ‘How many male partners have you had sex with after diagnosis?’, ‘How many of them are regular (or casual) partners?’ and ‘How often have you used condoms with your regular male partners during the last 3 months?’

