### Participants

#### Eligibility criteria

The participant inclusion criteria are as follows: 1) male, aged ≥18; 2) HIV-positive; 3) ART-naïve, and planning to initiate ART on the day of recruitment; 4) self-reported to be HIV-infected through homosexual transmission; 5) having access to the Internet on a smartphone; 6) having a WeChat account and using it in daily communication; 7) willing to provide written informed consent. Participants who have been hospitalized due to severe opportunistic infections are excluded.

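### The only partner-number wording given counts from HIV diagnosis; if used at follow-up, the count includes pre-randomisation partners and cannot fall

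*Protocol article*

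**What the plan says.** Under Secondary outcomes, the protocol article states that sexual risk behaviour "before and after diagnosis is measured separately using self-constructed items, including numbers of male/female and regular/casual partners, and frequency of condom use". The items shown are introduced by "Example items include". The partner items are "How many male partners have you had sex with after diagnosis" and "How many of them are regular (or casual) partners"; the second refers back to the partners counted in the first, so it shares the same window. The condom item has a different window: "How often have you used condoms with your regular male partners during the last 3 months".

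On timing, Eligibility criteria require a participant to be "ART-naïve, and planning to initiate ART on the day of recruitment" and set no limit on time since diagnosis. Data collection lists among the baseline variables "HIV status (transmission route, duration after diagnosis, sexual orientation, sero-status disclosure, STDs". Recruitment, enrolment and randomization places allocation after the baseline assessment.

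Data collection names sexual risk behaviour among the follow-up variables, with assessments at months 1, 3, 6 and 12, the last being six months after the intervention ends. Effectiveness of intervention gives sexual risk behaviours as an example of a binary outcome for the chi-square test and adds: "Within-subject analyses will also be conducted, comparing the baseline response to follow-up session responses".

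**The concern.** A randomised comparison of behaviour needs a recall period that starts at or after randomisation. The partner items instead start at diagnosis, an event that lies before randomisation by a different time for each participant. If the same question is asked at follow-up, each answer adds partners the intervention could not have influenced to those it could.

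Three things are then at stake. The baseline-to-follow-up comparison of the count could not show a reduction even if behaviour improved. The between-arm contrast, on a ratio or yes/no scale, would understate a real effect. At month 12 the count would pool the time before randomisation, the intervention period and the six months after it, so on its own it could not isolate a persistent effect.

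**Working it through.** **Plan's own figure.** The article gives no rate, standard deviation, effect or power for sexual risk behaviour, so there is nothing to reproduce. What follows shows the structure of the item and then an illustration on assumed inputs.

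**Structure.** Let *P* be partners between diagnosis and randomisation, and *C(t)* new partners from randomisation to time *t*. The item asked at *t* records *Y(t)* = *P* + *C(t)*.

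- *C(t)* cannot decrease, so *Y(t)* cannot. *Y(t)* minus the baseline answer is zero or positive.
- Randomisation gives *P* the same expectation in both arms, so the expected arm difference in *Y(t)* equals that in *C(t)*. The mean difference is unbiased.
- Adding *P* to both arms moves the ratio of means towards 1 and adds variance.
- Anyone with *P* ≥ 1 is a yes on an any-partner outcome at every visit, whatever the arm.

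**Illustration at month 6.** Assumptions, none from the article: *T* months from diagnosis to randomisation; a constant rate λ of new partners; a true 30% reduction after randomisation; person-to-person variation in the rate following a gamma distribution with shape 1 and mean 1. Evaluable number per arm: 300 × (1 − 0.20) = 240, borrowing the attrition stated for the adherence calculation.

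- Share of the window before randomisation: *T*/(*T* + 6).
- Apparent ratio: (*T* + 6 × 0.7)/(*T* + 6). For *T* = 3 this is 7.2/9 = 0.80.
- Any-partner risk difference: 1/(1 + λ(*T* + 4.2)) − 1/(1 + λ(*T* + 6)). For λ = 0.2 and *T* = 3 this is 1/2.44 − 1/2.80 = 0.410 − 0.357 = 5.3 points.
- Power of a two-sided 5% t-test on the counts: by simulation.

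| *T* (months) | Share before randomisation | Apparent ratio | Any-partner difference, λ = 0.2 (points) | Power, λ = 0.2 | Power, λ = 0.5 |
|---|---|---|---|---|---|
| 0 | 0% | 0.70 | 8.9 | 78% | 90% |
| 0.5 | 8% | 0.72 | 8.1 | 72% | 85% |
| 1 | 14% | 0.74 | 7.4 | 67% | 80% |
| 3 | 33% | 0.80 | 5.3 | 47% | 57% |
| 6 | 50% | 0.85 | 3.5 | 31% | 37% |
| 12 | 67% | 0.90 | 1.8 | 17% | 19% |

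The simulated any-partner differences were 9.0, 8.1, 7.2, 5.2, 3.4 and 1.9 points, in line with the formula. The mean difference does not depend on *T*: 0.2 × 6 × 0.3 = 0.36 partners, or 0.5 × 6 × 0.3 = 0.90. A count over a 3-month window after randomisation keeps the ratio at 0.70, with power of about 60–62% (λ = 0.2) or 81–82% (λ = 0.5).

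**Condom item.** A 3-month look-back lies wholly after randomisation at months 6 and 12 and roughly matches follow-up at month 3. Only at month 1, if it is asked then, do about two of its three months fall before randomisation.

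**The case against.** The strongest reply is that the defect is conditional. The quoted items are examples, and the article does not say which is asked at which visit; Table 3, which might settle it, is not in the text available. A before/after-diagnosis split fits a baseline questionnaire well. This stands: use at follow-up is an inference. It is a reasonable one, because the diagnosis split is part of the outcome's description and no other partner-number window is given.

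A reader might infer that every measure of effect is diluted. The documents do not support that, because randomisation balances the earlier partners and leaves the mean difference unbiased. A reader might also infer that the whole sexual-risk outcome is a running total; the condom item is not. Nor does the article say that the binary outcome tested by chi-square is derived from the partner count, or name partner counts in its sentence on within-subject analysis.

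The size is open too. The article reports no time since diagnosis, and its Background says national guidance since 2016 suggests immediate treatment for all, which points to shorter intervals. At half a month the ratio moves only from 0.70 to 0.72, and power falls by about 5 to 6 points.

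Finally, much is recoverable by subtraction if the same item was asked at baseline. Sexual behaviour is also only one of several secondary outcomes and is not named in the statement of the study aim. Both points stand and limit the weight of the finding.

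**Conclusion.** The point holds conditionally. If the diagnosis-anchored wording is used at follow-up, partner counts include pre-randomisation partners and, with accurate reporting, cannot fall. That makes them unsuitable for within-subject comparison and blunts ratio and binary contrasts between arms.

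The size cannot be fixed from the article. It runs from slight at half a month since diagnosis to an apparent ratio of 0.90 for a true 0.70 at twelve months, under a constant partner rate and a 30% true reduction. The power figures rest further on the assumed partner rates and their spread. The difference in mean counts loses precision but is not biased. The condom item is affected at month 1 only, if at all, and the two primary outcomes are untouched. This is a worthwhile, inexpensive improvement to a secondary outcome.

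**What to change.** State the follow-up wording and give partner numbers a fixed window after randomisation: for example, the last 3 months at months 3, 6 and 12, matching the condom item, and since enrolment at month 1. Apply the month-1 window to the condom item as well if it is asked then. Keep the before/after-diagnosis split for describing participants at baseline.

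For participants already assessed with the current wording, analyse the follow-up count minus the baseline count, and month 12 minus month 6 for the post-intervention period, wherever the same item was asked at both visits. Do not use the cumulative count for within-subject comparison.

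The cost is a wording change to a few online questions and one derivation rule. There are three downsides:

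- The dataset will hold two item versions. They do not measure quite the same thing: a windowed count includes a continuing regular partner again at each visit, whereas a difference of accurate running totals does not.
- A difference score also carries the recall error of both reports, including possible recounting of a regular partner.
- A 3-month window covers less time than the full six months. At 0.2 partners per month, its power for the mean difference (about 60–62%) is no better than that of the running total when time since diagnosis is one month or less (67–72%). The gain there lies in interpretability and in an undistorted ratio. A count since enrolment, or the follow-up-minus-baseline count, keeps the full period.
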